### Study sites

The FRANI pilot test is targeted to adolescent girls from 12 to 18 years old living Accra, Ghana and Thai Nguyen, Vietnam. These sites were selected based on relevance of the dietary quality concern and proximity to research partners.

### Inclusion and exclusion criteria, and recruitment

A total of 72 adolescents girls aged between 12 and 18 years will be randomly selected from two schools, one in each city, which staff has a good working relationship with our team. Those who assented for participation and which parents consented will receive a smartphone pre-configured with the FRANI app. Participants will be free to discontinue study participation at any time. Candidates will be excluded from the study if they do not provide assent or their parents do not provide consent to participate.

### Randomization and allocation

A computer-generated random number will randomize participants in the intervention and control groups at a 1:1 ratio for each country separately. The allocation sequence will be generated and the enrollment and assignment will be done by the senior researchers of the Vietnamese and Ghanaian teams. Although a similar description of FRANI will be presented for intervention and control groups in the process of informed assent and consent, it will not be possible to blind who is receiving feedback from FRANI and who is not. The data will be collected by the application without assessors.

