## Methods and analysis

### Materials

The pilot studies are based on two-armed randomized controlled designs to be implemented in Ghana and Vietnam. In each country, 36 adolescents (12–18 years) will be randomly allocated into two groups: The intervention group with the full version of FRANI, including diet records and nudges to encourage healthier food choices. The control group will receive mobile phones with FRANI functionality limited to the dietary assessment. Participants in both groups will have their food choices tracked for a four week period. The control group will then switch to also use FRANI with full functionality and both groups will be tracked for a further 2 weeks to assess acceptability, adherence, and usability. The schedule of the intervention, enrollment and assessment is described in Figure 1. The stylized program impact pathway for the intervention is described in Figure 2 (21).

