**Usability**
This app is simple to understand
I felt comfortable using this app
I felt praised when I ate healthy foods
I felt supported by my app friends
I can take pictures of my meals at home
I can take pictures of my meals in school
I can take pictures of my meals when I am eating with my family
I can separate what I eat from what others are eating to take pictures
I trust this app's feedback about my diet
I trust this app's information about healthy eating

Responses are in Likert scale from 1 = strongly agree to 5 = strongly disagree.

Based on the analysis of the program theory, the effects of the FRANI and gamified nudges on the dietary quality of adolescent girls will be assessed on a set of secondary outcomes including the percentage of meals recorded and the quality of food choices. The quality of food choices will be measured according to the Dietary Diversity Score (DDS) and the Sustainable Healthy Diet Score (SHDS). Adherence, percentage of meals recorded, the DDS and the SHDS will be measured using data captured by FRANI. Although the secondary outcome measures will be based on intervention and control group comparisons, the primary measures will not.

The data for outcomes will be recorded on FRANI and uploaded to a data collection platform at real time during the intervention period. Data collection will happen automatically once the participants took pictures of the foods they ate and confirmed their recognition. Since the image recognition technology from FRANI has been shown to be promising in the validation study (not published yet), the automatization of the data entry process may minimize mistakes if compared to other forms of food consumption data collection such as 24 h recalls and food frequency questionnaires. Baseline variables such as parents occupation, household assets and school performance will be collected with questionnaires. The data will be stored in protected clouds at the Pennsylvania State University.

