### Statistical analysis

The data from the pilot studies from Ghana and Vietnam will be analyzed and reported separately, though a pooled analysis will also be undertaken once both pilots have been completed. The analysis will be by intent to treat, and we do not expect to have loss of follow-up as this is a small scale pilot. Descriptive statistics and balance tables will be calculated for all variables and will be presented as medians or means with standard deviations. Differences in the outcomes between intervention and control groups will be estimated by multi-level Poisson regression models with the DDS and the SHDS as outcomes, a dummy variable for the treatment, a continuous time variable for the days and an interaction of treatment and time, and random effects at the individual level to account for the repeated measures. We will also undertake exploratory analysis for each food group of the DDS and the SHDS separately using odds ratio regressions. Socio-demographic variables that were not balanced after randomization will also be included in the robustness analysis.

A *p*-value < 0.05 will be considered statistically significant and *p*-value < 0.1 will be considered marginally significant. We will assess the need to screen outliers values greater than three standard deviations and will analyze the sensitivity of the treatment effect to the outliers.

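### Country is the only stated stratum for 36 girls aged 12–18, and adjustment waits for observed imbalance; two age bands with a prespecified term would protect the secondary diet contrasts at little cost

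*Protocol article*

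**What the plan says.** The Materials section fixes the size: "In each country, 36 adolescents (12–18 years) will be randomly allocated into two groups". The recruitment section gives the source: "A total of 72 adolescents girls aged between 12 and 18 years will be randomly selected from two schools, one in each city". Randomization and allocation gives the method: "A computer-generated random number will randomize participants in the intervention and control groups at a 1:1 ratio for each country separately". Country is the only stratum named. The same section has the senior researchers of each country team generate the sequence, enrol and assign, and states that blinding is not possible.

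Under Statistical analysis, the countries are reported separately, with a pooled analysis to follow. The multi-level Poisson models for DDS and SHDS are listed with treatment, day, their interaction and an individual random effect. Age is not among the listed terms. Imbalance is handled in two steps: "Descriptive statistics and balance tables will be calculated for all variables", and then "Socio-demographic variables that were not balanced after randomization will also be included in the robustness analysis". No criterion for imbalance is stated.

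On baseline data, the Outcomes section says: "Baseline variables such as parents occupation, household assets and school performance will be collected with questionnaires". Age is not among these examples, although the list is open-ended. On which outcomes depend on the arms, the same section says: "Although the secondary outcome measures will be based on intervention and control group comparisons, the primary measures will not". The Sample size section uses the four-week DDS and SHDS effects to size a larger experiment.

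**The concern.** Ages 12 to 18 cover a wide span of development. The Introduction describes adolescence as a time of rapid growth, rising nutrient needs, new responsibility for food and strong peer influence. It speaks of adolescence as a whole and gives no gradient within 12–18, but it is reasonable to expect a 12-year-old and an 18-year-old to differ in diet and in how they use the app.

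With 18 girls per arm in each country, chance alone can leave the arms different in age. The stated plan neither prevents this in the allocation nor fixes an age term in the main model. It lets the observed balance decide which variables are added, and then only in a secondary analysis. At stake are the precision and face validity of the DDS and SHDS contrasts, and of the effect size carried into the next trial.

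**Working it through.** The protocol gives no power calculation and no probability of imbalance, so there is no figure of its own to reproduce.

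**Inputs.** From the protocol: 36 girls per country, ratio 1:1, ages 12–18, countries reported separately. At exact 1:1 this is 36 / 2 = 18 per arm. Assumed, because the document gives no age distribution: (a) whole-year ages uniform on 12–18, SD = √((7² − 1)/12) = 2.0 years; (b) ages clustered around 15, SD about 1.2 years.

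**Standardised gap in mean age, one country.** SE = √(2/18) = 0.333 SD.
- Above 0.25 SD: z = 0.25/0.333 = 0.75, two-sided probability 45%. Simulation (100,000 runs) gives 46% under either age distribution.
- Above 0.5 SD: z = 1.5, probability 13%. Simulation gives 14%.

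**At least one of two separately reported countries** (normal approximation). Above 0.5 SD: 1 − (1 − 0.134)² = 25%. Above 0.25 SD: 1 − (1 − 0.453)² = 70%.

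**Pooled, 36 per arm.** SE = √(2/36) = 0.236 SD. Above 0.25 SD: 29%. Above 0.5 SD: 3%.

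**In years, and with two age strata.** Simulated for 18/18 allocation with no age stratum, and for a younger and an older half each split 9:9:

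| | No stratum, SD 2.0 | No stratum, SD 1.2 | Two strata, SD 2.0 | Two strata, SD 1.2 |
|---|---|---|---|---|
| SD of the gap (years) | 0.67 | 0.40 | 0.35 | 0.24 |
| P(gap ≥ 0.5 year) | 48% | 21% | 18% | 4% |
| P(gap ≥ 1 year) | 15% | 1% | 0.5% | about 0% |
| P(gap > 0.25 SD) | 46% | 46% | 16% | 22% |
| P(gap > 0.5 SD) | 14% | 14% | 0.5% | 1.2% |

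**As shares.** Suppose 18 of the 36 girls are in the younger band. The number x allocated to one arm is hypergeometric: P(x) = C(18,x)·C(18,18−x)/C(36,18).
- 11 against 7 or worse, a gap of at least 4/18 = 22 points: 31.8%.
- 12 against 6 or worse, a gap of at least 6/18 = 33 points: 9.4%.

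**What this could mean for DDS.** The document gives no slope of DDS on age. At an assumed 0.05–0.2 points per year, a gap of one SE shifts the contrast by 0.67 × 0.05 = 0.03 to 0.67 × 0.2 = 0.13 points (SD 2.0), or 0.40 × 0.05 = 0.02 to 0.40 × 0.2 = 0.08 points (SD 1.2), on the 0–10 scale. This illustrates scale and is not an estimate.

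**The case against.** The case against acting is substantial, and most of it stands.

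- **Chance imbalance is not bias.** Randomisation already counts it as sampling error. What is lost is precision and some credibility.
- **The primary outcomes are untouched.** Adherence, acceptability and usability are not compared between arms. Only secondary contrasts in a budget-sized pilot are affected.
- **The plan already responds to imbalance.** It foresees balance tables and an adjusted robustness analysis. That analysis is planned in advance, although its covariates are chosen from the data.
- **The model has a treatment-by-day interaction.** A stable age-related difference in diet level would fall mainly on the treatment main effect and less on the difference in slopes.
- **Choosing age is partly a matter of judgement.** Household assets or school performance could also be argued for.

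A reader might also infer several stronger things that the document does not support:

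- **That the randomisation is unrestricted.** The text names no block or other restriction, but it does not exclude one, and an article may leave that detail to the full protocol. Coin-toss allocation would give exactly 18/18 in only C(36,18)/2³⁶ = 13% of draws; the text does not say this is the method.
- **That ages are known from a school list before selection.** Age must be established for eligibility, but the document does not say when, or whether all girls are allocated at once.
- **That imbalance could match any plausible four-week diet effect.** No expected effect, DDS variability or age slope is given, so this cannot be shown.

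What survives is narrower. The stated allocation has no age stratum, the listed main model has no age term, and adjustment depends on observed imbalance with no stated criterion.

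**Conclusion.** The point holds as a minor, inexpensive improvement. It is not an error or a contradiction in the protocol.

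It would be tempting to say that a sizeable age imbalance is likely, but the figures do not support that. In each country a modest gap (above 0.25 SD) is close to a coin toss at about 46%, and a larger one (above 0.5 SD) is about one in seven. Whether that amounts to a year depends on the unknown age spread: about 15% if ages are uniform and about 1% if they cluster. Two age strata would cut the chance of a gap above 0.5 SD from about 14% to about 1%.

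The consequence is limited to precision in the secondary DDS and SHDS contrasts and in the effect size passed to the larger trial. Its size cannot be fixed from the document, because the relation between age and diet is not given. The probabilities rest on 18 per arm and on the two assumed age distributions.

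**What to change.** 1. Once the consented girls and their ages are listed, allocate each country in a single balanced draw within two age or grade bands (for example 12–14 and 15–18), giving 18/18 overall to within one girl.
2. Do not use small permuted blocks filled in sequence. The same unblinded researchers generate, enrol and assign, so later allocations within a small band would be partly predictable to them. One draw on a complete list avoids this.
3. Record age as a baseline variable and prespecify the age band as a term in the main DDS and SHDS models, replacing imbalance-triggered adjustment for age. The robustness analysis can remain for other variables.

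Cost: a few lines in the randomisation program, one model degree of freedom, and a list that must be complete before anyone is allocated. No additional girls or staff are needed, and the only data needed is age, which eligibility already requires.

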### Outcomes

The feasibility of FRANI will be assessed by measuring outcomes related to adherence, acceptability, and usability as summarized in Table 2 (25, 26). According to the World Health Organization (WHO), adherence is “the extent to which a person's behavior – taking medication, following a diet, or executing lifestyle changes, corresponds with agreed recommendations from a health care provider” (27). Although there is no consensus in the literature on the best measure for adherence to eHealth technology interventions (25, 26), maximum benefit from the intervention as defined by creators should be considered (28). We define the sample adherent to FRANI if 70% or more of participants-days upload complete dietary recalls in the last two weeks of the pilot study. Acceptability summarizes likeability and satisfaction with FRANI, while usability summarizes what affects the use of the FRANI. Acceptability and usability are measured according to answers from structured questionnaires described in Table 3. If participants grade the acceptability or usability of FRANI as 30 or less points in their respective structured questionnaires, the app will be considered accepted or usable.

**Table 2 T2:** Domains and outcome measures for the FRANI pilot test.

Outcomes	Definition
Primary outcomes (feasibility)	
Adherence	The number of days participants upload completed dietary recalls on the FRANI divided by the total number of dietary recalls (complete + incomplete) of the last two weeks of the pilot test is equal to or higher than 70%
Acceptability	Summarizes likeability and satisfaction with FRANI according to answers from a structured questionnaire. If participants grade the acceptability of FRANI as 30 or less points on a scale from 10 to 50 points, the app will be considered accepted.
Usability	Summarizes possibility to use and intent to keep using FRANI according to answers from a structured questionnaire. If participants grade the usability of FRANI as 30 or less on a scale from 10 to 50 points, the app will be considered usable.
Secondary outcomes	
Percentage of meals recorded	The number of meals recorded on the FRANI divided by the number of total meals participants had during the last two weeks of the pilot test period.
Dietary Diversity Score^a^	Ranges from 0 to 10 points using MDDW dietary diversity food groups (daily score) measured in the first four weeks of the pilot study period.
Sustainable Healthy Diet Score^b^	Ranges from 0 to 14 points using EAT-Lancet food groups (daily score) measured in the first four weeks of the pilot study period.

^a^
The dietary diversity score was calculated according to the Minimum Dietary Diversity for Women, A Guide for Measure (26).

^b^
The Sustainable Healthy Diet Score was calculated according to the study EAT- Lancet Score and Major Health Outcomes: The EPIC-Oxford Study (25).

**Table 3 T3:** Questionnaire about acceptability and usability of the FRANI application.

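### Table 2's adherence ratio omits days with no upload and contradicts the participant-days rule in the text, so a largely unused app could pass the 70% mark

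*Protocol article*

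**What the plan says.** The Outcomes section of the protocol article defines adherence twice.

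- **Text:** "We define the sample adherent to FRANI if 70% or more of participants-days upload complete dietary recalls in the last two weeks" of the pilot. The unit is the participant-day.
- **Table 2, Adherence row (under primary outcomes):** the numerator is "The number of days participants upload completed dietary recalls on the FRANI", and it is "divided by the total number of dietary recalls (complete + incomplete) of the last two weeks of the pilot test". The pass mark is again 70%.

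Three other statements bear on the point. The later part of the Outcomes section says that data are captured automatically once a participant has photographed her food and confirmed the recognition. The recruitment section says "Participants will be free to discontinue study participation at any time". Table 2 also lists the share of meals recorded, over the same two weeks, as a secondary outcome with no threshold.

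The article does not define a complete or an incomplete recall, and it does not say which of the two adherence rules prevails.

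**The concern.** The two denominators are different quantities. Participant-days are fixed by design: every enrolled girl contributes 14. Recalls exist only if the girl starts one. Under Table 2 as worded, a day without any upload is neither a complete nor an incomplete recall, so it disappears from the ratio. So do all the remaining days of a girl who stops using the app or leaves the study. Table 2 also divides days by recalls, which is a proportion only if there is at most one recall per day.

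The behaviour that an adherence measure should detect, not using the app, therefore cannot lower the Table 2 figure. Adherence is a primary outcome with a fixed pass mark, and the Abstract and Discussion link a larger trial to the results of this pilot. A favourable adherence finding could thus rest on a minority of active users. Having two rules also leaves room to choose between them after the data are seen.

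**Working it through.** **Inputs**

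- Participants: "In each country, 36 adolescents" (Materials); 72 in total (recruitment section).
- Window: the last two weeks, 14 days (Materials; Outcomes).
- Pass mark: 70% under both rules (Outcomes text and Table 2).
- Share of days with an upload, and share of uploads that are complete: not given in the article. The values below are assumptions, shown over a range.

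The 70% mark is a chosen criterion, not a derived figure, so there is no calculation in the plan to reproduce.

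**Formulas**

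Let C be the participant-days with a complete recall, I the incomplete recalls and n the number of participants. Let s be the share of participant-days with any recall and q the share of recalls that are complete, with one recall per day.

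- Text rule: C / (14n) = s × q
- Table 2 rule: C / (C + I) = q

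The two agree only when s = 1. If s is below 70%, the text rule cannot be met even when every upload is complete, while Table 2 can still be met.

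**What the text rule requires**

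- Per country: 36 × 14 = 504 participant-days; 0.70 × 504 = 352.8, so 353 complete days (353/504 = 70.04%).
- Pooled: 72 × 14 = 1008; 0.70 × 1008 = 705.6, so 706 complete days.
- Table 2 sets no minimum number of upload days.

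**Illustration (assumed s = 50%, q = 80%)**

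- Recalls: 0.50 × 504 = 252. Complete: 0.80 × 252 = 201.6, about 202.
- Table 2: 202/252 = 80%, pass.
- Text: 202/504 = 40%, fail.

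**Fewest complete days that pass Table 2, per country**

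| Assumed share of days with a recall | Recalls | Complete days needed | Table 2 | Text rule |
|---|---|---|---|---|
| 100% | 504 | 353 | 70.0% | 70.0% |
| 90% | 454 | 318 | 70.0% | 63.1% |
| 75% | 378 | 265 | 70.1% | 52.6% |
| 50% | 252 | 177 | 70.2% | 35.1% |
| 20% | 101 | 71 | 70.3% | 14.1% |

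**Limiting case:** one girl uploads on all 14 days, 10 of them complete, and the other 35 upload nothing. Table 2 gives 10/14 = 71.4%, which passes; the text rule gives 10/504 = 2.0%.

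The rules can disagree at moderate non-use too. With s = 80% and q = 80%, Table 2 gives 80% and the text gives 64%. With s = 80% and q = 90% the text gives 72% and both pass.

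**The case against.** The strongest reply is that an incomplete recall was meant to include a day with no upload. If each participant-day is one daily recall, complete or not, then Table 2's denominator is all participant-days and the two rules coincide. The numerator, which counts days, fits that reading and would also remove the mixed units. But the article never says so, a count of recalls does not naturally include recalls that were never started, and the description of data capture points the other way. If this was the intention, the text still needs to say it.

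It can also be said that Table 2 is only a summary and the explicit rule in the text governs. That is reasonable, but the article does not state it, and Table 2 is worded as a definition with its own pass mark.

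Three points stand as limits on the concern:

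- Partial recording does lower the Table 2 ratio; only days with no upload at all escape it.
- The share of meals recorded would reveal an unused app. However, it is secondary, has no threshold and does not enter the adherence verdict.
- The article sets no formal progression rule based on the 70% mark, and reminders, local monitoring and the expectation of no loss to follow-up suggest that use may be high. The illustrations show what the rule permits, not what is likely. An expectation of no loss to follow-up also does not cover an enrolled girl who simply stops photographing meals.

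**Conclusion.** The concern holds. One primary outcome has two conflicting definitions, and the one in Table 2, read as written, is insensitive to non-use. The two figures differ by the factor s, the share of participant-days with any recall. At an assumed s of 50%, Table 2 can be passed with about 35% of participant-days complete, against the 70% that the text requires; at 75% the figure is about 53%.

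The contradiction and the formulas need no assumption beyond one recall per day and the literal reading that a day without an upload creates no recall. The size of any discrepancy in this pilot depends on upload rates that the article does not give. Because the conflict can reverse the stated conclusion on a primary outcome, it should be resolved before the adherence data are analysed.

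**What to change.** Use one definition in the text and in Table 2: the number of participant-days with a complete recall, divided by all participant-days in the last two weeks (504 per country, 1008 pooled). State that days with no upload, and days after a girl discontinues, stay in the denominator and count as not complete. Define a complete and an incomplete recall.

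Two additions would help but are not needed to correct the error. One is a 95% confidence interval that allows for clustering of days within participants. The other is a descriptive split by randomised arm, because in this window the control arm is in its first two weeks on the full version while the intervention arm is in weeks 5 and 6.

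The cost is a short edit to Table 2, with the definitions added, and no new data. Reported adherence may be lower than under the present Table 2 wording.

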**Figure 2 F2:**
[figure not shown]
The stylized program impact pathways for the FRANI. (Source: Adapted from (21)) Notes: Yellow represents the two steps users have to follow to have their dietary consumption tracked and to be nudged to make healthier food choices. Green boxes show nudges to influence the use of the FRANI and healthy food choices. Blue boxes represent what is expected to improve with the FRANI use. Gray is for a possible unintended consequence of the FRANI use that should be fixed in future versions of the app.

The main differences in the application versions for the intervention and control groups are described in Table 1. Briefly, both the intervention and control versions of FRANI recognize food images, assess the quality of the user's diet, and receive notifications with reminders to take pictures. However, only the treatment group can set food consumption goals, see the home screen, scores and statistics about dietary quality, receive badges and receive a daily report summarizing everything they ate in that day.

**Table 1 T1:** Features of FRANI by intervention group in the first four weeks of the pilot study.

Feature	Intervention	Control
Meal entry (picture taking)	X	X
Recognize food image in pictures	X	X
Assess quality of user's diet	X	X
Notifications	X	X
Setting goals	X	NA
Home screen	X	NA
Scores and statistics	X	NA
Medals and badges	X	NA
Daily report	X	NA
Activity feed	X	Modified
Daily report	X	NA

NA, not available. At the end of the fourth week, the control group switches to the intervention version and all participants use the same version of FRANI for two weeks to measure adherence, acceptability and usability.

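### Percentage of meals recorded is meant to show the effect of the nudges by arm, but its window falls in the two weeks when both arms use the full app

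*Protocol article*

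**What the plan says.** All references are to the Protocol article.

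- **Purpose.** The Outcomes text after Table 3 says that the effects of FRANI and its nudges "will be assessed on a set of secondary outcomes including the percentage of meals recorded and the quality of food choices". It then sets the type of analysis: "Although the secondary outcome measures will be based on intervention and control group comparisons, the primary measures will not".
- **Definition and window.** Table 2 defines percentage of meals recorded as "The number of meals recorded on the FRANI divided by the number of total meals participants had during the last two weeks" of the pilot. In the same table the other two secondary outcomes, the Dietary Diversity Score (DDS) and the Sustainable Healthy Diet Score (SHDS), are measured in the first four weeks.
- **Timeline.** Materials gives the randomised phase: "Participants in both groups will have their food choices tracked for a four week period". It continues: "The control group will then switch to also use FRANI with full functionality and both groups will be tracked for a further 2 weeks". The footnote to Table 1 confirms that, after the switch, "all participants use the same version of FRANI for two weeks to measure adherence, acceptability and usability".
- **Data source.** The Outcomes text states: "Adherence, percentage of meals recorded, the DDS and the SHDS will be measured using data captured by FRANI". It adds that collection is automatic once a participant has photographed her food and confirmed what was recognised. Randomization and allocation says that no assessors are involved.

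**The concern.** The between-arm purpose and the measurement window do not fit together. The arms differ in app version only in the first four weeks, and this outcome is measured only in the last two. Of the three secondary outcomes in Table 2, it alone lies outside the randomised contrast.

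Two things are at stake. First, a difference or a null result in weeks 5-6 could be reported as evidence about the nudges when it is not. Second, the same outcome measured in weeks 1-4 would be useful for reading the diet scores. DDS and SHDS are daily scores built from what participants photograph. Table 1 gives goals, scores, badges and daily reports to the intervention arm only, and these features could prompt more photographing as well as better eating. Fuller recording can raise a food-group count with no change in diet. Table 2 defines no recording rate by arm for weeks 1-4 that would help separate the two explanations. The Sample size section plans to use the DDS and SHDS effect sizes to size a larger trial, so a recording artefact could carry forward.

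A smaller concern is the denominator. Total meals eaten includes meals that were never photographed, and the article names no source for those apart from FRANI itself.

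**Working it through.** The plan gives no figure for this outcome to reproduce. The check is timeline arithmetic, followed by a sensitivity calculation for the denominator.

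**1. Window against randomised contrast**

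Inputs: four weeks of full versus limited FRANI, then two weeks with everyone on the full version (Materials; Table 1 footnote; Figure 1 caption, which gives 28 days); outcome window in the last two weeks (Table 2).

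- Study length: 28 + 14 = 42 days.
- Randomised full-versus-limited period: days 1-28. Outcome window: days 29-42.
- Days in common: 0 of 14.

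**2. What the arms differ by in days 29-42**

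| | Intervention | Control |
|---|---|---|
| Days on full version before day 29 | 28 | 0 |
| Days on full version by end of day 42 | 28 + 14 = 42 | 0 + 14 = 14 |

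The intervention arm moves from 4 to 6 weeks of full-version use and the control arm from 0 to 2. The version in use is the same, so the contrast is prior exposure: early against delayed access.

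**3. Effect of moving the window**

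With the outcome defined over days 1-28, the overlap becomes 28 of 28 days. Per country the participant-days available are 36 x 28 = 1,008, against 36 x 14 = 504 in the present window. No sample size or power figure changes, because the sample size was set by budget.

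**4. Denominator**

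*Case A: meals counted only from FRANI's own meal records.* Every meal in the denominator is then a recorded meal, so the ratio is recorded / recorded = 100% for every participant with any record. A girl who eats 4 times and photographs 2 has a true rate of 2/4 = 50% but would show 2/2 = 100%.

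*Case B: an assumed number of meals per day.* The documents give no such number. As an assumption, take 2 to 5 meals a day over 14 days and a participant with 24 recorded meals:

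| Meals per day (assumed) | Total meals | 24 / total |
|---|---|---|
| 2 | 28 | 85.7% |
| 3 | 42 | 57.1% |
| 4 | 56 | 42.9% |
| 5 | 70 | 34.3% |

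The same record gives anything from 34.3% to 85.7%, so the source of the total matters as much as the recording.

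*Limit of a simple fixed count.* If 3 meals a day were the denominator and every record counted, a girl who recorded 4 a day would score 4/3 = 133%. A fixed count needs a cap of one record per meal slot.

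**The case against.** **It may really be a feasibility measure.** It shares its window with adherence, and Statistical analysis names regression models only for DDS and SHDS. The general sentence about secondary outcomes may have caught it by accident. This is plausible, and it lowers the severity. It does not remove the conflict, because the Outcomes text names this outcome explicitly among those that assess the effects of the nudges. On that reading it is the Outcomes text that has to change.

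**The weeks 5-6 comparison is still randomised.** This stands. A reader might infer that the comparison must be null because both arms use the same version. The documents do not support that: carry-over, novelty or fatigue could produce a real difference. The comparison answers a different question from the one stated.

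**The denominator may be handled elsewhere.** A condensed article can leave operational detail to a fuller document. The section on the intervention mentions information that users upload as well as pictures, and the adherence definition separates complete from incomplete recalls. A reader might infer that FRANI cannot observe total meals at all. That goes beyond the text: it is a well-supported inference from the stated capture process, not a documented fact. What stands is that neither of these statements supplies a count of meals eaten, and the source should be named.

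**Recording in the first four weeks is not lost.** A reader might infer that it goes unmeasured. It does not: both arms are tracked from the start and data are uploaded in real time. What is missing from the article is a recording rate defined as an outcome for that period.

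**Conclusion.** The point holds, at moderate severity. As written, percentage of meals recorded cannot estimate the effect of full versus limited FRANI, because its window shares 0 of 14 days with the period in which the arms use different versions. What it compares is about 4-6 against 0-2 weeks of full-version exposure. This rests only on the stated timeline and on the stated between-arm use of the outcome.

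The denominator is a secondary point and is conditional: the ratio is exactly 100% if total meals come only from FRANI's meal records, and the article does not say that they do. The 34.3% to 85.7% range rests on an assumed 2 to 5 meals a day and illustrates sensitivity only.

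A reader might infer a threat to the pilot's main conclusions. The documents do not support that. The primary feasibility outcomes are not arm comparisons, no model is specified for this outcome, and only DDS and SHDS feed the sizing of the later trial. The link to those scores is through their interpretation.

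**What to change.** 1. In Table 2, define the between-arm version of percentage of meals recorded over the first four weeks (days 1-28), the window already used for DDS and SHDS. Report it by arm beside those scores, to help judge whether a difference in them reflects more complete recording.
2. Keep the last-two-weeks figure as a descriptive feasibility measure with no arm comparison.
3. Amend the Outcomes text so that its statement about between-arm comparison covers the first and exempts the second.
4. State where total meals come from. The source should not depend on recording and should be the same in both arms. One approximate option is a fixed number of main-meal slots set in advance, counting at most one record per slot so that the figure cannot exceed 100%.

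The cost of items 1 to 3 is wording: FRANI captures recorded meals from the first day, and the sample size is unaffected. Item 4 may need a small addition to data collection if a source other than fixed slots is chosen. Fixed slots cost nothing to collect, but they ignore skipped and extra meals. If the nudges change how often girls eat, equal denominators will not remove that bias, and the report should say so.
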